##### Analyses of process indicators

To portray adherence to the single prevention measures and the nvHAP bundle as a whole a descriptive analysis will be performed, summarizing continuous and intermittent process indicators and the ‘nvHAP overall adherence score’ by department-level periods. Further, we will evaluate whether the process indicators are associated with the nvHAP incidence rate. We will use GEEs with Poisson error and departments as clusters (as described above) to model the monthly nvHAP rates as dependent on either single continuous process indicators or on all continuous process indicators combined.

To model monthly nvHAP as dependent on intermittent process indicators (either single process indicators, all process indicators combined, or the nvHAP overall adherence score), we will use GEEs with Poisson error and departments as clusters (as described above). Because the intermittently collected process indicators are collected only at four time points, we will use linear interpolation to derive monthly values for these process indicators.

#### Qualitative analysis

Longitudinal qualitative data from drop-in, action-plan and focus group interviews will be included in a cross-case analysis, where each participating department represents a case. In a first step, all interview transcripts and notes will be coded deductively using the Theoretical Domains Framework (TDF) as a coding scheme as well as additional codes to capture our pre-defined implementation outcomes [23]. Inductive thematic analysis will then be conducted to identify themes relevant to the implementation within TDF domains. Analyses will begin with at the case level to understand the local influencers of implementation at the department level, allowing us, for example, to assess how implementation outcomes shift over time in relation to the undertaken interventions and in light of local barriers and facilitators. Then, cross-case matrices will be used to explore any trends across departments [31]. This qualitative analysis will allow us to make a qualitative assessment about which local factors and interventions contributed to implementation success. Our in-depth findings will also help to ultimately shine light on quantitative study results. The researchers involved in qualitative analysis will engage in an ongoing process of *reflexivity* [29], considering the role of our own preconceptions and close relation to the implementation process, while also aiming to provide an authentic account of the implementation process.

## Discussion

With this mixed-methods study we will close critical knowledge gaps about the prevention of nvHAP, a neglected but common HAI. To date, literature about prevention measures against nvHAP is scarce [4], and our study will provide further knowledge by assessing the effectiveness of a five element prevention bundle against nvHAP on lowering nvHAP incidence rates. To our knowledge, it is the first study testing an inpatient bundle of nvHAP prevention measures on a broad patient population. Moreover, as effective implementation is as important as choosing the right bundle elements [14, 32], we place focus on a theoretically-informed implementation strategy.

The quantitative part of the study aims to not only measure the primary outcome parameter nvHAP incidence rate over time, but to also measure process indicators. This will help us to better understand if the implementation process was successful and to evaluate direct association between prevention measures and nvHAP incidence rate. As the nvHAP bundle cannot be effective if it is not well implemented, it is important to also measure implementation outcomes (e.g. acceptability, appropriateness, fidelity, and sustainability) as necessary preconditions for achieving the desired changes in clinical outcomes.

A major strength of this study is the mixed-methods approach, including an extensive formative qualitative study to provide insights about how and why departments succeeded, or faced challenges, in implementing the nvHAP bundle. With some notable exceptions [33–36], many qualitative implementation evaluations are limited to inquiries conducted at a single point in time. Such inquiries are prone to participant recall biases and may be insufficient to telling the whole implementation story [26]. Our longitudinal qualitative study aims to provide critical contextual insights to guide others hoping to implement the nvHAP bundle. Additionally, the participatory approach of our formative evaluation is intended to increase project commitment among stakeholders, particularly local implementation teams.

The limitations of our study are the following: First, our study does not include a control group. We abstained from conducting a randomized controlled trial due to anticipated high contamination between departments/wards within the same hospital. Second, the duration of the implementation period is determined to be 2 months not accounting for possibly longer duration due to the formative approach of the implementation strategy. We aim to address this point by analysing the results both on the hospital and department level. Third, by continuously collecting process indicators from EMR, we cannot preclude reporting bias (e.g. increased documentation of oral care). We address this issue by additionally measuring process indicators on an individual basis. Further, although we take efforts to demonstrate empathic neutrality during our qualitative data collection, we cannot entirely preclude the possibility that qualitative researchers may be perceived as being partial, leading to potential desirability bias in the qualitative data. Finally, we acknowledge that our formative process evaluation does in itself lead to changes in implementation plans and that these changes must be documented with great care to keep track of the exact implementation activities. Rather than purely a limitation, we view this as a strength of our study, and we anticipate that it should also be integrated into recommendations for those wishing to replicate results of our future nvHAP study.

In conclusion, with this innovative mixed-methods study design, we will assess the effectiveness of the nvHAP bundle, but also measure process indicators of the nvHAP bundle and contextual factors influencing implementation uptake. We will be able to triangulate our findings, i.e. correlate nvHAP rates with adherence data of the prevention bundle and again with qualitative measures of implementation success. Further, our mixed-method approach will be of great value to understanding the complex contextual interactions that influence implementation success, which are necessary to inform implementation guidance for other institutions planning to implement the nvHAP bundle.

Addendum: Due to the COVID-19 pandemic, the study data collection had to be terminated earlier than planned (i.e. end of February 2020). Additional file 7 informs about the details of early study termination.

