The nvHAP study team, based in the infection prevention department, will form a central coordinating team to provide local teams with support, example training materials, and feedback on process and outcome data. Additionally, we will employ a formative approach, during which we aim to continuously identify influences on implementation efforts (e.g. barriers and facilitators) and feed these insights back to local implementation teams to optimize the potential for implementation success [25]. This formative evaluation will occur in stages throughout the project, as described by Stetler and colleagues [25] and presented in Table 1. The formative evaluation will rely primarily on “action plan” meetings as an opportunity to feed information back to local implementation teams regarding identified barriers and facilitators to implementation and to refine implementation action plans accordingly.

**Table 1 Tab1:** Formative Evaluation Stages

Stage	Aims	Concretization in current study
1. **Developmental evaluation, “diagnostic analysis”**	Assess levels of current practices and their determinants Prospectively identify potential barriers and facilitators to implementation	During the baseline period “Action Plan” interview with local implementation teams, the current state of practice for each nvHAP bundle measure will be assessed and determinants of current behaviour discussed. An “Action Plan” of promotional activities will be established, taking into account potential barriers and facilitators.
2. **Implementation-focused evaluation**	Assess discrepancies between established implementation plan and its operationalization Continually identify barriers and facilitators to implementation Refine implementation plan	During the “Action Plan” interview with local implementation teams following the implementation period, the previously established “Action Plan” will be revisited and actual vs. planned interventions assessed. Refinements to the action plan will be made as needed taking into account newly identified barriers and facilitators.
3. **Progress-focused evaluation**	Monitor and inform stakeholders about progress towards goals	During the Intervention period, feedback about nvHAP outcomes and process indicators will be fed back to local implementation teams.

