#### Study periods on department and hospital level

Baseline period will start at the same time for all departments and will be of different length (minimum 12 months) as implementation of nvHAP prevention measures will occur at the department level and the start of implementation activities is chosen by every department, primarily relying on availability of resources.

We define three study periods on the *department level*, 1) department baseline period, before implementation of nvHAP bundle in the specific department; 2) department implementation period, a two month time frame starting with the beginning of implementation activities in the respective department; 3) department intervention period following the department implementation period.

On the *hospital level* the three periods are defined as follows: 1) hospital baseline period, before starting implementation in the first department; 2) hospital implementation period, from the beginning of the implementation period of the first department until end of implementation period of the last included department; 3) hospital intervention period following the hospital implementation period. Figure 2 depicts an anticipated study timetable.

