### Analysis

#### Quantitative analysis

##### Analyses of nvHAP bundle effectiveness

To evaluate the effectiveness of the intervention bundle, two distinct analyses are performed. First, a change point model will be combined with piecewise constant rates with additional sine-cosine waves to account for seasonality. Poisson regression (with log link function) is used to analyse the monthly overall nvHAP incidence rate over all departments, using the monthly sum of the nvHAP cases over all departments as “count” and the monthly sum of the number of patient days (in thousands) over all departments as offset. Study period on the hospital level (hospital baseline, implementation, intervention period) will be used as explanatory factor (see Additional file 6 ‘Statistical analysis’ for detailed statistical model). We may use a quasi-poisson model in case of overdispersion.

Second, a longitudinal Poisson regression will be used. The monthly number of nvHAP cases in each department will be modelled by a generalized estimating equation (GEE) with departments as clusters. This allows to account for the non-independence of consecutive nvHAP counts within departments, to model the temporal correlation structure (e.g. first order autoregressive) and to account for over-dispersion, if necessary. We will assume a Poisson error distribution for the nvHAP counts and use the log link function. As above, we may use a quasi-Poisson model in case of overdispersion. We will use a time-dependent, department-specific binary indicator variable for department-level implementation of the intervention bundle (possibly with an intermediate level for the implementation phase) as explanatory variable. Further, we will adjust for seasonality of nvHAP incidences by inclusion of sine/cosine waves.

Because the baseline period includes nvHAP rates from 2017 which served (inter alia) as basis for the choice of the nine departments, we will perform sensitivity analyses excluding data from 2017 for all analyses described above to assess a potential “regression to the mean” effect.

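### Analysing at both hospital and department level only partly answers the concern that the fixed two-month implementation window is too short

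*Protocol article*

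**What the plan says.** The section on study periods fixes the "department implementation period, a two month time frame starting with the beginning of implementation activities in the respective department". At the higher level it defines the "hospital implementation period, from the beginning of the implementation period of the first department until end of implementation period of the last included department". Each department chooses its own start, mainly according to resources.

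The effectiveness analysis has two models. The pooled Poisson model uses the hospital periods: "Study period on the hospital level (hospital baseline, implementation, intervention period) will be used as explanatory factor". The department-level GEE uses a department-specific, time-dependent indicator, "possibly with an intermediate level for the implementation phase". The one sensitivity analysis stated for these models leaves out the 2017 data.

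Table 1 (formative evaluation stages) has the action plan revisited after the implementation period: "Refinements to the action plan will be made as needed taking into account newly identified barriers and facilitators". It places feedback of outcomes and process indicators in the intervention period.

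The limitations paragraph of the Discussion concedes that "the duration of the implementation period is determined to be 2 months not accounting for possibly longer duration due to the formative approach" and continues: "We aim to address this point by analysing the results both on the hospital and department level".

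**The concern.** The article names a specific weakness, a transition window that may be too short, and offers a specific answer. The question is whether the answer tests the weakness.

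Table 1 schedules refinement of the roll-out in months that the department-level model codes as full intervention. If uptake is still rising in those months, the department-level rate ratio averages ramp-up with established practice and lies closer to 1 than the ratio under established practice. At stake is the size of the primary effect. A reader of the results could also take agreement, or disagreement, between the two analyses as evidence about the window when it is not clean evidence.

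**Working it through.** **Which months each analysis sets aside.** The article gives no effect size, build-up time or spacing of starts in its text, so there is no stated figure to reproduce. The definitions give the structure directly. Let a department start k months before the last one.

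- Department level: 2 months set aside, for every department.
- Hospital level: k + 2 months between its own start and the first hospital intervention month, because the hospital period runs "until end of implementation period of the last included department".

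For the last department k = 0, so it gets 2 months in both analyses. If all departments start together, k = 0 for all and the windows are identical. The extra run-in is therefore a by-product of scheduling, not a chosen length.

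**What else differs.** The hospital baseline stops at the first department's start, while each department baseline runs to that department's own start. One model pools monthly counts; the other is a GEE clustered by department. A difference between the two results thus mixes window length, baseline months and model.

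**Size, by illustration.** All of the following are assumptions except the nine departments and the two-month window, which come from the article: starts every 2 months at months 13, 15, …, 29; data to month 38; equal department sizes; true rate ratio 0.70; log effect rising linearly to full at R months after the start, evaluated at mid-month.

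Rate ratio at t months after the start = 0.70^min(1, t/R), averaged over the department-months coded as intervention.

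*Department-months coded as intervention.* With a two-month window, a department starting at month s contributes 37 − s months: 24, 22, …, 8, in total 9 × (24 + 8)/2 = 144. With a six-month window it contributes 33 − s: 20, 18, …, 4, in total 108. At hospital level, months 31 to 38 count for all nine: 8 × 9 = 72.

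*Worked case, R = 6.* After a two-month window, each department has four partly implemented months (t = 2.5, 3.5, 4.5, 5.5) with ratios 0.8619, 0.8122, 0.7653 and 0.7211, which sum to 3.1605.

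- Department level: (9 × 3.1605 + 108 × 0.70)/144 = 104.04/144 = 0.723.
- Hospital level: only the last department (four months) and the one before it (two months, 0.7653 and 0.7211) are still building up. (3.1605 + 1.4864 + 66 × 0.70)/72 = 50.85/72 = 0.706.

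| Analysis | Department-months | R = 6 | R = 9 | R = 12 |
|---|---|---|---|---|
| Department level, 2-month window (planned) | 144 | 0.723 | 0.747 | 0.772 |
| Hospital level (planned) | 72 | 0.706 | 0.718 | 0.734 |
| Department level, 6-month window (proposed check) | 108 | 0.700 | 0.711 | 0.733 |

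**Sensitivity to the assumptions.** A second illustration gives each department 12 intervention months after the two-month window. The department-level ratio is then 0.730 for R = 6 and 0.796 for R = 12. The hospital-level ratio is 0.706 and 0.740 with starts one month apart, and equals the department-level value with no stagger. With only 6 intervention months the department-level ratio is 0.760 and 0.863, so shorter follow-up increases the dilution.

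**The case against.** A reader might infer that neither analysis changes the window and that the limitation is left unaddressed. The documents do not support that. The hospital-level period sets aside more than two months for every department that starts before the last. In the staggered scenario above, the hospital-level result lies within 0.001 to 0.007 of what a six-month department-level window would give. The Discussion also speaks only of an aim, inside a list of limitations.

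Three further points have weight.

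- The bias is toward the null. It cannot produce a false benefit, and it needs both a working bundle and uptake beyond two months.
- The study tests bundle and implementation strategy together. The average rate after a fixed start-up is a legitimate effect of the two as rolled out, and later refinement of the action plan is part of the design.
- The planned GEE models of monthly rates on process indicators relate outcome to actual adherence and so partly capture gradual uptake.

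The detailed statistical model is in an additional file that is not shown, and it could contain runs with other windows. The absence of such runs from the article is therefore not the point.

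What remains is the sentence itself. It offers as the answer an analysis whose benefit depends on the order of starts, is nil for the last department and vanishes without stagger. The adherence models are not put forward as the answer to this limitation.

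**Conclusion.** The point holds in a limited form. Analysing at both levels removes part of any dilution when starts are staggered, but it does not test the two-month assumption, and the difference between the two analyses does not isolate window length.

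In the main scenario a true ratio of 0.70 reads as about 0.72 to 0.77 at department level and 0.71 to 0.73 at hospital level. These figures rest on the assumed ratio, a linear build-up of the log effect over 6 to 12 months, equal department sizes and starts two months apart; the article gives none of these. The effect is modest for a moderate build-up and larger with slow uptake or short follow-up. The addendum on early termination makes shorter follow-up possible, but the details are in a file not shown. This is a cheap improvement to the interpretation of the primary outcome, not a flaw that invalidates the analysis.

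**What to change.** 1. Keep two months as the main definition of the department implementation period.
2. Make the intermediate implementation level in the department-level GEE definite.
3. Add sensitivity runs of that model with the implementation level lengthened to 4 and to 6 months, or with the intervention period split into early and later months.
4. Reword the limitation: the hospital-level analysis lengthens the run-in only for departments starting before the last and so addresses the point in part, and the sensitivity runs examine window length directly.

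The cost is two further runs of an existing model and one reworded sentence, with no new data. The downside is fewer intervention months, mostly felt in late-starting departments, and hence wider intervals in those runs. In the illustration a six-month window leaves 108 of 144 department-months, and the last department keeps 4 of 8.

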## Data Availability

Data sharing is not applicable to this article as no datasets were generated or analyzed during the current study.

## Abbreviations

CFIR: Consolidated Framework for Implementation Research
ECDC: European Centre for Disease Prevention and Control
EMR: Electronic medical record
GEE: Generalized estimating equation
HAI: Healthcare-associated infections
HAP: Hospital-acquired pneumonia
ICU: Intensive care unit
MSA: Modified swallowing assessment
nvHAP: Non-ventilator-associated hospital-acquired pneumonia
PPI: Proton pump inhibitors
TDF: Theoretical Domains Framework
UHZ: University Hospital Zurich
VAP: Ventilator-associated pneumonia
